## Abstract

**Purpose:**

Automated insulin delivery (AID) systems are the gold standard for managing type 1 diabetes (T1D), yet access remains inequitable due to funding disparities, workforce limitations, bias, and geographic barriers. The ACCESS-AID study aims to implement a new model of care by using a remote ‘Hub’ to deliver prioritised training and support to those most in need and to improve workforce capacity by working in partnership with New Zealand’s National Public Health service.

**Methods:**

Eligible participants include all individuals with T1D and eligible people with pancreatogenic/Type 3c diabetes). Enrolment will use a prioritisation score. After informed consent and baseline assessments, participants receive one-day AID training (in-person or remote) by certified, industry provided trainers, followed by 12-weeks of structured support from Hub staff. The primary outcome is implementation effectiveness. Secondary outcomes: clinical and psychosocial impacts, safety, nutrition education effectiveness, and qualitative insights. CGM metrics and HbA1c will be assessed at baseline and 12-weeks, and CGM again at 24-weeks. Hub staff will receive training in AID management, complete self-efficacy assessments, and participate in interviews.

**Conclusion:**

This model offers a novel, scalable and equity-focused approach to diabetes technology care, which will enhance outcomes for people with diabetes and inform future service delivery for other long-term conditions.

## Background

Automated insulin delivery (AID) systems are globally recognised as the gold standard for managing glucose levels in people with type 1 diabetes (T1D) [1, 2]. These systems link an insulin pump, continuous glucose monitor (CGM) and computer algorithm to semi-automate insulin delivery. AID systems have been shown to greatly improve glycaemic outcomes [3]. For example, in a randomised controlled trial of children and youth aged 7 to 25 years with above-target glycemia, HbA1c decreased by 2.5% (95% CI −3.1 to 1.8 [−27mmol/mol, 95% CI −34 to −20] *p* < 0.001) and time in range (TIR) increased by 35% (95% CI 28 to 41%) after using AID for 13-weeks, compared to the control group (multiple daily injections or continuous subcutaneous insulin infusion) [4].

Despite this evidence, in Aotearoa New Zealand (herein referred to as NZ) and worldwide, access to these advanced diabetes technologies is slow and inequitable [5–7]. Until recently in NZ, the main barriers to access included the lack of publicly funded CGM and restrictive eligibility criteria for insulin pump funding and consumables particularly for adults, people from low socioeconomic backgrounds, or ethnic minorities [5] with similar trends observed worldwide [8]. However, in October 2024, funding in New Zealand was expanded to include CGM and pumps for all people with type 1 and related forms of diabetes, enabling broader use of AID systems. Despite advances in technology and liberalisation of funding, many barriers to access remain. Historical treatment guidelines prioritised those who had more in-target glycemia and diabetes management skills [9, 10], effectively gatekeeping this technology from individuals who experience the greatest absolute benefits. Furthermore, workforce constraints, and sometimes overly complicated training and support pathways remain key barriers [11, 12] with evidence from the UK highlighting funded practitioner time as a key barrier for supporting individuals to use this technology [13]. Now more than ever, there is an urgent need to provide efficient and equitable access to AID for the thousands of individuals estimated to seek this technology in the coming years.

Although global evidence supports the use of telehealth for effective management of both diabetes [14] and other chronic disease [15, 16], particularly to improve patient access [17, 18], uptake of telehealth models has been slow. Diabetes nursing telehealth services are just as effective as standard care models with evidence for sustained glycaemic improvements [19] demonstrating the potential for this model of care. However, current telehealth models have been limited to ongoing management rather than initiation of new technology. The Accelerating Care, Capacity and Equity in Automated Insulin Delivery Systems for New Zealanders with Type 1 Diabetes (ACCESS-AID) Study, aims to simplify AID training by utilising a remote health care team to prepare and support individuals regardless of their physical location, to begin AID following structured online patient education, and a highly effective in-person, single day training session provided by certified pump trainers. This approach aims to efficiently and safely speed up training and access to AID, and has been used previously by our research team to successfully train high-risk and priority populations across the lifespan onto AID systems [20–23]. Furthermore, evidence from our research group indicates that access to modern diabetes technologies is an effective equaliser of ethnicity-based disparities in diabetes outcomes, and thereby is an effective equity tool [6, 24]. Therefore, the ACCESS-AID study will use a prioritisation score to ensure equitable access to overcome some of the documented barriers in the current health care system.

This study will also include a ‘train-the-trainer’ model, which is an effective method for knowledge and clinical practice dissemination [25, 26], whilst also being cost-effective and able to be moulded to local requirements [27]. Clinical staff, such as registered nurses, physicians, pharmacists and dietitians from existing diabetes related health services will be seconded to the ACCESS-AID Hub, during which time they will be provided with training and support to gain confidence and skills related to AID management. This is important as a lack of knowledge and confidence in T1D advanced technologies has been identified as a barrier to access [28, 29]. Therefore, while the aims are to improve efficiency and equity of access to technology, this study will also mentor and train staff to increase capacity throughout the public health system. Furthermore, as previous success in AID has undoubtedly been supported by the fact that the recipients of AID are within a research project receiving close support and attention [23, 30], it is important to evaluate whether we can safely integrate these training models into standard clinical care to support existing teams and training methods.

This study builds on our wider research groups’ portfolio of experimental studies and moves this work into the implementation phase to bring this new model of care into mainstream clinical practice. This study is being conducted in partnership with Health New Zealand/Te Whatu Ora, the national public health care provider, and aims to deploy a novel national remote “hub” model (herein referred to as the Hub), to prioritise access to AID for those with greatest need. This new model of care is designed to specifically address the well documented barriers to access [29, 31–33], with a specific focus on priority populations living with T1D such as those living rurally, Māori and Pacific peoples, those with less in-target glycemia and/or more diabetes-related complications. Furthermore, we anticipate that this model of care may provide a framework for the management of other areas of diabetes care, or other chronic conditions, both nationally and worldwide.

### Objectives

This study has four main objectives: (1) To determine the effectiveness and safety of a remote Hub to start AID and address inequities in care; (2) To investigate using qualitative methodologies whether the Hub is acceptable for both people and whānau (families) living with T1D and their health care teams, and how the model can be improved; (3) To determine whether inviting diabetes care providers to partake in the Hub is effective in improving knowledge about, and training methods for AID; (4) To determine the cost effectiveness of the Hub in starting AID compared to current models across districts in NZ.

## Methods

### Trial conduct

#### Study design

This is a quasi-experimental, single-arm study which will assess a new model of AID health care delivery in NZ. The new model of health care will be the remote Hub which will be deployed to provide prioritised national AID set up and support, before transferring participants back to their usual care teams after a maximum of 12 weeks (See Fig. 1 for summary of study design). The duration from referral to enrolment may vary depending on participants prioritisation score (outlined below in Sect. 2.3.2).

**Fig. 1 Fig1:**
[figure not shown]
ACCESS-AID study design summary

#### Design of remote hub

The Hub will be staffed by a multidisciplinary clinical team from various regions across NZ. Clinical staff members will be registered nurses/diabetes nurse specialists ideally with prescribing authorisation. Endocrinologists and other allied health professionals involved in the care of patients with T1D (e.g., prescribing pharmacists and dietitians) will also be part of the team. Most direct participant contact will be conducted by the nursing and allied health staff (as compared to endocrinologists). Those working in primary care may also be employed to staff the Hub. Appropriate supervision will be provided.

#### Consent

Participants will be sent an email/text to complete online informed consent using REDCap (REDCap software, Research Electronic Data Capture, production server version 14.3.0, Vanderbilt University, Nashville, TN, USA). The email, and online portal will have a copy of the participant information sheet. If unable to be completed online, a copy of the participant information sheet and consent forms will be sent via post to the participant to complete. Participants will be encouraged to discuss participation with their whānau (family) and usual care providers, and to contact the research team with any questions prior to providing informed consent.

### Study population

All people with T1D, and people with pancreatogenic or Type 3c diabetes who meet the public funding access criteria for an insulin pump and CGM [34], will be eligible to participate. Speed of access will be based on their prioritisation score. Furthermore, interested people must have a suitable health care team (determined by study clinical staff) who are available and willing to provide ongoing care to the person with diabetes once their participation in the study is complete. Existing healthcare teams will be notified when their patient has been enrolled and updated throughout their time enrolled in the Hub. Individuals who are pregnant will not be eligible to participate as these individuals will be prioritised through existing health delivery pathways. Additionally, those who have non-diabetes related, active moderate-to-severe health and/or mental health issues, will be referred to appropriate health care providers first for support and management, before transitioning to diabetes technology (at the discretion of the clinical team). In situations where additional requirements are identified, eligibility will be assessed on a case-by-case basis to ensure safety and support of transitioning to AID (for example, severely impaired vision or recent acute medical event).

#### Recruitment

Interested individuals may be referred from any primary or secondary care provider in NZ (through word of mouth and dissemination within the wider research teams clinical networks), or interested individuals can approach the study team directly. The referral form will include a range of required information including demographics, recent anthropometric measurements, diabetes history and relevant clinical history. Regardless of method of referral, the study team will confirm agreement from participants’ usual diabetes health care provider for ongoing care after AID training and discharge from the study team.

### Procedures

#### Intervention

All participants enrolled in the study will receive the intervention as this is a single-arm study. Once enrolled, participants will be supported to start an AID system and be followed up over a period of 12 weeks (see study schedule in Table 1).

**Table 1 Tab1:**
[figure not shown]
ACCESS-AID study schedule

#### Prioritisation score

Data collected from the referral form will be used to calculate a prioritisation score (Table 2). Given the substantial waiting lists for AID access across NZ, the prioritisation score is designed to ensure current inequities in access to AID are addressed and those who may benefit the most are prioritised.

**Table 2 Tab2:** Study prioritisation framework

Priority items:	Potential Score
Māori and/or Pacific ethnicity	2 points
HbA1c > 86 mmol/mol (10%) ^1^	2 points
Living rurally ^2^	1 point
HbA1c 58–85 mmol/mol (7.5 to 10%)	1 point
Severe hypoglycaemia in last 2 years	1 point
Age < 25 years ^3^	1 point
Known diabetes complications	1 point
Occupational requirement (e.g. driver/shift worker)	1 point
**Potential total**:	**10 points**

^1^HbA1c target is < 53mmol/mol (the above target those who are less healthy)

^2^Rurality defined using participants home address and the Geographical Classification of Health [35]

^3^Younger age – due to longer potential life with diabetes and risk of complication over time

Based on assessment of the prioritisation score, and study capacity, individuals will be invited to enrol in the Hub via email or phone.

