### Statistical analysis

Pharmac, NZs pharmaceutical funding agency, estimates there are 18,000 to 21,000 people with pancreatic insufficiency (mostly T1D) living in NZ who would be eligible for funded CGM [11], of whom 85–90% were not using AID in 2023. We believe the Hub will facilitate approximately 500 new AID starts per year (provided by 2.4 full time equivalent clinical staff, per year).

A sample size of 500 or more participants will provide > 90% power, with a two-sided alpha of 0.05, to detect small changes in continuous outcomes (effect sizes ≥ 0.15) and estimate binary outcomes to within +/- 5%.

Numbers of people referred to the Hub, enrolled, and started on AID will be tabulated by the key demographic and clinical variables required for calculation of the prioritisation score as listed under Sect. 2.5.1.

Incidence proportions, stratified by region and priority subpopulations, will be calculated as the number of AID starts divided by the number of eligible people not on AID as estimated from national administrative datasets. For comparisons with other providers, an individual will be considered to have started on AID on the date they are first dispensed a subsidised pump as recorded by Health New Zealand.

Interrupted time series analysis will be used to investigate the impact that the Hub has on the rate of new AID starts nationally, and by region, Absolute numbers and incidence proportions of new AID starts will be calculated for consecutive time periods and displayed graphically. Generalised linear (Poisson) regression models will be used to estimate changes in the in the numbers and incidence of new AID starts before versus after deployment of the Hub. Differences between regions, such as workforce capacity, may be explored in models to identify facilitators and barriers to AID uptake.

Intervention effectiveness will be confirmed by descriptively summarising changes in Hub participants’ HbA1c and CGM metrics before versus after starting on AID.

National laboratory and CGM data is not available for those not enrolled in the study.

Incidence rates of adverse events will be calculated for study participants after AID start and compared to control populations utilising generalised linear regression models, adjusting for demographic factors (age, gender, ethnicity, NZ deprivation index). Controls will included study participants prior to AID start and non-study people with type one diabetes who have and have not started on AID.

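### Table 2 leaves an HbA1c of exactly 86 mmol/mol in neither scoring band, so such a referral ranks below one at 58; separately, the stated total of 10 cannot be reached

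*Protocol article*

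**What the plan says.** Table 2, under Prioritisation score in the Protocol article, lists eight scoring rows and a potential total of 10 points. Two rows concern HbA1c:

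- 2 points: "HbA1c > 86 mmol/mol (10" per cent)
- 1 point: "HbA1c 58–85 mmol/mol (7.5 to 10" per cent)

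The other six are "Māori and/or Pacific ethnicity" (2 points) and, at 1 point each, "Living rurally", "Severe hypoglycaemia in last 2 years", age below 25 years, "Known diabetes complications" and "Occupational requirement (e.g. driver/shift worker"). The article gives no rule for boundary values or for rounding between units.

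The score is used in practice. Study population says that it sets the speed of access. Prioritisation score says that it determines, together with study capacity, who is invited. Study design says that the interval from referral to enrolment may depend on it. In Statistical analysis, the counts referred, enrolled and started are to be "tabulated by the key demographic and clinical variables required for calculation of the prioritisation score".

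**The concern.** The upper band starts strictly above 86 and the lower band stops at 85, so 86 itself belongs to neither. Read literally, the HbA1c points rise, drop to zero at 86, and rise again. That cannot be intended in a score meant to move people with more to gain up the queue. The two units also disagree: the table pairs 86 mmol/mol with 10%, and the 1-point row includes 10%.

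At stake is a person's place in the queue. A loss of 1 point equals the whole weight of rurality, and a loss of 2 equals the weight of ethnicity.

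The total is a second and separate matter. It counts both HbA1c rows although no single result can satisfy both.

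**Working it through.** **Inputs.** All scoring inputs come from Table 2: the two HbA1c rows with their limits and percentages, the six other rows with their points, and the stated total of 10.

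**Step 1: reproduce the stated total.** Adding all eight rows in table order gives 2 + 2 + 1 + 1 + 1 + 1 + 1 + 1 = 10. The figure is therefore a plain column sum.

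**Step 2: the attainable maximum.** The six non-HbA1c rows give 2 + 1 + 1 + 1 + 1 + 1 = 7. The HbA1c rows are disjoint (above 86, or 58 to 85), so one person earns at most 2 from them. The maximum is 7 + 2 = 9, in either unit.

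**Step 3: HbA1c points around the boundary.** The table pairs 58 with 7.5% and 86 with 10%. The straight line through those pairs is % = 7.5 + (x − 58) × 2.5/28, rounded to one decimal for scoring.

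| HbA1c (mmol/mol) | Points by the mmol/mol limits | Table's own % equivalent | Points by the % limits |
|---|---|---|---|
| 57 | 0 | 7.4 | 0 |
| 58 | 1 | 7.5 | 1 |
| 85 | 1 | 9.9 | 1 |
| 86 | 0 | 10.0 | 1 |
| 87 | 2 | 10.1 | 2 |

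In mmol/mol the points run 1, 0, 2 at 85, 86 and 87. In per cent they run 1, 1, 2. With every other item met, a person at 86 totals 7 + 0 = 7 in mmol/mol and 7 + 1 = 8 when read as 10%. An otherwise identical person at 58 totals 8.

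**Step 4: the loss at 86.** If 86 was meant for the lower band, the loss is 1 − 0 = 1 point. If it was meant for the upper band, the loss is 2 − 0 = 2 points.

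**Step 5: how many referrals.** The documents give no HbA1c distribution for referrals, so this step is an assumption. Take results as whole numbers from a normal distribution with mean m and SD s. The share reading 86 is Φ((86.5 − m)/s) − Φ((85.5 − m)/s).

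- m = 70, s = 18: Φ(0.917) − Φ(0.861) = 0.820 − 0.805 = 1.5%
- m = 75, s = 20: Φ(0.575) − Φ(0.525) = 0.717 − 0.700 = 1.7%
- m = 80, s = 20: Φ(0.325) − Φ(0.275) = 0.627 − 0.608 = 1.9%

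The extreme pairings within those ranges move this only slightly: m = 70 with s = 20 gives Φ(0.825) − Φ(0.775) = 1.4%, and m = 80 with s = 18 gives Φ(0.361) − Φ(0.306) = 2.1%. If laboratories report decimals, every value above 85 and up to 86 falls in the gap, not only the single whole number.

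**The case against.** The strongest reply is that very little follows from this. One whole-number value is uncovered. Table 2 leads with mmol/mol and nothing says that scoring is ever done in per cent, so the conflict between units may never arise in use. The study is single-arm, so the score allocates no treatment, and all who meet the criteria stay eligible. All of that stands, and it limits the point. It does not remove the gap, because the gap exists in mmol/mol alone, and invitation depends on score and capacity. When places are short, a lost point can mean a later invitation.

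A reader might infer more than the documents support:

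- **That the unreachable total misranks people.** It does not. Everyone is scored on the same rows, and the order is the same whether the footer reads 9 or 10.
- **That thresholds on the score are shifted.** The article sets no cut-off, quantile or category on the score.
- **That the analysis tables inherit the hole.** Statistical analysis tabulates by the variables behind the score. It does not say that HbA1c will be banded as in Table 2, and the recorded value at 86 remains available. The time-series, incidence, safety and glycaemic analyses and the power statement are not described as using the score.
- **That the share in the last step gives a head count per 500.** The 500 in Statistical analysis is expected AID starts per year. The score applies to referrals, whose number is not given.

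A cumulative reading (1 point plus a further 2 above 86) would rescue the total of 10, but the printed upper limit of 85 on the 1-point row rules it out.

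**Conclusion.** The point holds in two parts of unequal weight. The first is a real defect in a working rule: as written, a referral at exactly 86 mmol/mol scores 0 for HbA1c, below a referral at 58 and in conflict with the table's own percentage. It is ranked 1 or 2 points too low. That follows from the printed limits alone. Its reach is small: about 1.5 to 1.9% of referrals under the three assumed distributions, and 1.4 to 2.1% at the extremes of the same ranges. The documents supply no distribution to test this against.

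The second is a labelling error: the maximum is 9, not 10, with no effect on anyone's rank. Neither part is shown to bias an estimate or alter the power statement. The case for correction is that the rule is wrong as printed, affects the order of access, and is easily repaired.

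**What to change.** Reconcile the two HbA1c rows so that 86 mmol/mol (10%) falls in exactly one band and the limits agree in both units. Which band it joins is for the sponsor to decide. State how decimal values between 85 and 86 are treated. If the rows stay mutually exclusive, restate the potential total as 9. Rescore any referral already scored with an HbA1c of 86, and check whether its place in the queue changes.

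The cost is a small edit to Table 2 and to whatever tool applies the score, which the article does not describe, plus a check of what is likely to be a small share of referrals. No analysis or sample size needs to change.

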#### Baseline

After completing consent, participants will then be directed to complete a range of online questionnaires (or on paper if unable to be completed online) including the diabetes treatment satisfaction questionnaire (DTSQ), EQ-5D, and the carbohydrate counting assessment tool.

If a participant has not had a routine biochemical review completed as part of their usual diabetes care in the past 12 months, a referral will be sent to the relevant laboratories where the participant is located for collection of samples to assess: urinary albumin: creatinine ratio, lipid and/or renal studies. A request for an updated HbA1c will be sent for all participants (either laboratory or point of care). Anthropometric data (weight, height and blood pressure) included in the referral will be used as baseline data.

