#### 12-weeks (primary end-point)

At 12 weeks, participants will be asked to complete the DTSQ change and EQ-5D questionnaires, and to attend their nearest laboratory for a final measurement of HbA1c. CGM data will be downloaded from participants’ online profile. Access to participant profiles will be retained on the study accounts to allow for remote review at 6-months for the purpose of data retrieval. Participants will be referred back to their usual care team at 12-weeks post AID start or earlier if stable (e.g., If TIR is > 70% or individualised TIR target is met with no significant hypoglycaemia or other concerns, the patient will be discharged before 12 weeks). This will involve a transfer of all CGM and HbA1c data back to their usual care teams to ensure optimal ongoing support. If for any reasons the Hub team do not believe discharge at 12 weeks is safe, then this will occur at a later date when appropriate.

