### Outcomes

The primary outcome of this study is to assess the implementation effectiveness of the Hub. Secondary outcomes of this study include intervention effectiveness, safety and acceptability, psychosocial measures, nutrition education effectiveness, cost-effectiveness and clinical staff self-efficacy and intervention acceptability.

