#### Intervention effectiveness

Intervention effectiveness of AID will be determined by estimating participants’ changes in standard glycaemic metrics between baseline and 12-weeks including: HbA1c, time in range ([TIR], 3.9 to 10.0 mmol/L [70 to 180 mg/dL]), time in tight range ([TING/TITR] 3.9 to 7.8 mmol/L [70 to 140 mg/dL]), time below range ([TBR] < 3.9mmol/L [< 70 mg/dL]), and time < 3mmol/L (< 54 mg/dL), > 10mmol/L (> 180 mg/dL) and > 13.9mmol/L (> 250 mg/dL). CGM metrics will also be assessed between baseline and 12-weeks, and again at 24-weeks (6 months) to determine whether any benefits are maintained following discharge, These include glycaemic management index (GMI), glycaemic outcomes differentiated as 24 h, day (0600–2359 h) and night (0000–0559 h), co-efficient of variation (CV_glucose_), and mean sensor glucose +/-SD.

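### HbA1c may be measured by laboratory or point of care at baseline but is sent to a laboratory at 12 weeks, so the change score carries any mean between-method difference for participants with a point-of-care baseline

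*Protocol article*

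**What the plan says.** The protocol article sets the HbA1c method separately at each visit.

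- **Baseline** (Procedures, Baseline): "A request for an updated HbA1c will be sent for all participants (either laboratory or point of care". Either method is acceptable.
- **12 weeks** (Procedures, 12-weeks (primary end-point)): participants are asked "to attend their nearest laboratory for a final measurement of HbA1c". Only a laboratory is named.
- **Use of the two values** (Outcomes, Intervention effectiveness): the outcome is "changes in standard glycaemic metrics between baseline and 12-weeks including: HbA1c", followed by the CGM metrics.
- **Tier** (Outcomes): "Secondary outcomes of this study include intervention effectiveness, safety and acceptability". HbA1c change is therefore secondary.
- **Analysis** (Statistical analysis): "Intervention effectiveness will be confirmed by descriptively summarising changes in Hub" participants before versus after AID start. The article describes no step that takes the assay method into account.
- **Comparator**: "This is a quasi-experimental, single-arm study" (Study design), and "National laboratory and CGM data is not available for those not enrolled in the study" (Statistical analysis). There is no concurrent or external HbA1c series.

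**The concern.** A before-and-after change is interpretable only if the measuring method stays the same or its difference is known. Here the stated procedures let the method switch for some participants. The switch can go only one way in order: point of care first, laboratory second. There is no provision for the reverse, so a mean difference between the methods would not average out across participants. A larger sample would narrow the interval around the shifted value without moving it.

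In a randomised comparison both arms would share the switch and it would largely cancel. This study has one arm and no outside HbA1c data, so any method difference is read as part of the change after starting AID. At stake is the accuracy of the reported mean HbA1c change, and its interpretation among participants whose baseline was point of care.

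**Working it through.** **The plan's own figure.** Statistical analysis states: "A sample size of 500 or more participants will provide > 90% power, with a two-sided alpha of 0.05", for effect sizes of 0.15 or more. Treated as a within-person change:

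- Power = Φ(0.15 × √500 − 1.96) = Φ(3.354 − 1.960) = 0.918 (0.917 with the noncentral t). The stated power is reproduced.
- The number needed for 90% power is 467.

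The sample size is not in question. The calculation assumes that the change is measured without systematic error.

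**What the method switch does.** Let b be the mean point-of-care minus laboratory difference, and p the share of analysed pairs with a point-of-care baseline and a laboratory 12-week value.

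- Mixed pair: observed change = laboratory value at 12 weeks − (laboratory-equivalent baseline + b) = true change − b, on average.
- Same-method pair: observed change = true change, on average.
- All pairs: mean observed change = mean true change − p × b.

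If point of care reads higher (b > 0), the fall in HbA1c is overstated. If it reads lower, the fall is understated.

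**Inputs.** The article gives none of p, b or the SD of change. The values below are assumptions, used only to show the range.

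Shift p × |b| in mmol/mol:

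| p | \|b\| = 1 | \|b\| = 2 | \|b\| = 3 | \|b\| = 5 |
|---|---|---|---|---|
| 10% | 0.1 | 0.2 | 0.3 | 0.5 |
| 25% | 0.25 | 0.5 | 0.75 | 1.25 |
| 50% | 0.5 | 1.0 | 1.5 | 2.5 |

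Within the mixed pairs alone the shift is the full |b|, here 1–5 mmol/mol.

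**Scale.**

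- Against sampling error: with N = 500 and an assumed SD of change of 10, 15 or 20 mmol/mol, the 95% half-width (1.96 × SD/√500) is 0.9, 1.3 or 1.8 mmol/mol. Most of the table lies inside this; its upper corner does not.
- Against the only HbA1c effect in the article: the Background cites a 27 mmol/mol difference from an earlier randomised trial. The range is 0.1/27 = 0.4% to 2.5/27 = 9.3% of that. That trial enrolled people aged 7 to 25 with above-target glycaemia. Eligibility here has no HbA1c threshold, so the mean change may be smaller and the percentage larger.

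**With matched methods.** p = 0, the method term disappears, and the power is unchanged at about 0.92.

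**The case against.** The strongest reply is that this is a small asymmetry in a descriptive secondary outcome. Most of that stands. The time-in-range measures, mean sensor glucose, the glycaemic management index and the coefficient of variation do not depend on the HbA1c assay, so a spurious HbA1c shift could be noticed against them. Every input to the size is assumed. Samples come from many providers and laboratories, and a net shift needs a common non-zero mean difference across them, which the article does not show.

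Three stronger readings are tempting, and the article does not support them:

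- *The bias has a known direction.* Only the order of the methods is fixed. The sign of b is not given.
- *The bias can match the smallest effect the study is designed to find.* The 0.15 SD figure is a generic power statement for continuous outcomes, not an HbA1c target, and no HbA1c test is specified. With an SD of change of 10–20 mmol/mol it equals 1.5–3.0 mmol/mol, which the shift reaches only at the upper end of the assumed ranges.
- *It distorts a rural comparison.* Greater point-of-care use in rural areas is an assumption. The article stratifies AID starts and prevalence by priority group, not HbA1c change. Its one between-group glycaemic comparison (Nutrition education effectiveness) uses 12-week values, when everyone is directed to a laboratory.

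It can also be said that Table 1 is not shown and that the full protocol may contain a matching rule. The concern, however, rests on two procedures the article does state, and they differ. Analysis can separate mixed pairs afterwards only if the method was recorded.

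**Conclusion.** The point holds as a modest design weakness. The stated procedures put any mean between-method difference into the HbA1c change of every participant with a point-of-care baseline and a laboratory 12-week value, and nothing in the single-arm design removes it. The shift in the overall mean is p × b. Under the assumed p of 10–50% and |b| of 1–5 mmol/mol it is 0.1–2.5 mmol/mol in either direction; the true size cannot be derived from the article. If the AID effect is large, the shift is unlikely to alter the conclusion. It would matter more if the mean change proved small, or if HbA1c change were later compared between groups that differ in point-of-care use. A reader should not infer that the effectiveness result is invalid, or that benefit is inflated.

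**What to change.** Amend two procedures and add one summary:

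1. In Baseline and in 12-weeks (primary end-point), state that the 12-week HbA1c uses the same method as that person's baseline where feasible: laboratory for both, or point of care repeated at 12 weeks.
2. Record the method (laboratory or point of care) with each HbA1c result.
3. Keep all pairs in the main HbA1c change summary, and add a sensitivity summary limited to same-method pairs.

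Point 3 is deliberate. Limiting the main summary to same-method pairs could drop participants for whom a laboratory is hard to reach, and a compulsory laboratory baseline would add an access step to a study meant to remove such barriers.

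The cost is one extra data field, one extra table, and point-of-care testing at 12 weeks for some participants. If matching proves impractical, points 2 and 3 alone still show how far the result depends on mixed pairs.
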